### Recruitment {15}

One hundred sixty patients are recruited from the Colorectal Surgical In-patient Department of CICMAS through publication and distribution of posters and leaflets containing information of the study.

### Assignment of interventions: allocation

#### Sequence generation {16a}

Randomized allocation sequence will be generated using Statistical Analysis System, SAS 9.3 (SAS Institute Inc. Cary, NC, USA), by an appointed investigator.

#### Concealment mechanism {16b}

The generated sequences will be placed in serialized, opaque, sealed envelopes (to ensure concealment of allocation from the evaluators).

#### Implementation {16c}

After ensuring patients fulfill inclusion criteria and informed consent forms are obtained from them, the envelopes are opened by the acupuncturist and acupuncture treatment is carried out (the acupuncturist is excluded from assessment and statistical analytic process as blinding of the acupuncturist cannot be achieved). The study group will be revealed at the same time to both the patient and researcher.

### Assignment of interventions: blinding

#### Who will be blinded {17a}

Throughout the study, the statisticians and evaluators are blinded, so that independent assessments and statistical analysis can be carried out. The subjects in the control group could not be blinded due to their particularity. Acupuncturists were not blinded in this study.

#### Procedure for unblinding if needed {17b}

Unblinding will only be allowed under emergencies such as the incidence of serious adverse effects.

### Data collection and management

#### Plans for assessment and collection of outcomes {18a}

The data will come from the electronic medical record (EMR) and will be collected using the case report form (CRF). A questionnaire survey was conducted by doctors. Laboratory tests are performed by the laboratory and all data obtained during the study will be anonymized and stored in the study folder on our protected study server. Only the research team has access to this particular research folder. The operation time, intraoperative rehydration, the use of anesthetics, the number of lymph nodes removed, and the length of hospital stay will be obtained from the EMR. In addition, the results of the quality of life scale (QLQ-C30) will be used to evaluate the postoperative quality of life.

#### Plans to promote participant retention and complete follow-up {18b}

The patients will receive extensive information about the study set-up and requirements during the recruitment. The importance of completion of the follow-up will be stressed. Patients are allowed to stop acupuncture at any time during the study and are not obliged to give a reason to discontinue. If possible, the patient will be asked to complete the survey at 1 month after acupuncture treatment. All patients are reminded throughout the study to fill out the questionnaires during study visits. Throughout the follow-up period, the researchers will check responses and, if necessary, contact patients for completion of their follow-up.

#### Data management {19}

Patient data will be collected through ECRF. QLQ-C30 will be filled in by telephone and will be stored in SPSS. Back-ups in the study folder on the protected research server will be made regularly (once per 1 month). Informed consent and end-of-trial dates will be recorded in the electronic patient dossier, and signed paper forms will be stored within our hospital in a locked room. (S)AE(I)s will be recorded in the eCRF. To be able to reproduce study results and to help future users to understand and reuse data, all changes made to the raw data and all steps taken in the analysis will be documented in the eCRF and IBM SPSS. Source data will remain available in the electronic patient record. All research data, including patient material, will be archived for 30 years after the study has ended.

#### Confidentiality {27}

Research data will be stored using a study identification code for each participant. The key to the identification code list will only be available to the research team during the study and will be documented and safeguarded by the principal investigator according to research guidelines after completion of the study. No patient identification details will be reported in publications.

Plans for collection, laboratory evaluation, and storage of biological specimens for genetic or molecular analysis in this trial/future use {33}

Not applicable. The biological samples collected in this study are only used as safety evaluation indicators and will not be used for genetic or molecular analysis. The biological samples will be destroyed immediately after monitoring, which will not infringe on the rights and interests of participants, let alone violate ethics.

### Statistical methods

#### Statistical methods for primary and secondary outcomes {20a}

Spss22.0 software was used to analyze and process the clinical observation data, in which in the descriptive statistical analysis, qualitative indicators were described by frequency table and percentage and quantitative indicators were described by mean and standard deviation. Comparison of the two groups was performed: quantitative data in line with normal distribution using the *t* test, homogeneity test of variance between groups, with 0.05 as the test level, uneven variance using Satterthwaite method for correction of *t* test, and not in line with normal distribution using Wilcoxon rank-sum test. The hypothesis test uses a two-sided test and gives the test statistics and the corresponding *p* value, with *p* ≤ 0.05 as statistically significant. All (S)AE(I)s will be summarized and recorded including the nature, date and time of onset, date of resolution, determination of seriousness, severity, action taken, outcome, and possible causality to study treatment. SAE data will be presented in a descriptive manner.

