#### Secondary outcomes

Secondary outcomes include the time of first postoperative defecation, time of first fluid intake, and time of first ambulation, which are obtained through the assistance of family members and caregivers, via inquiry and records of patient’s status. Other secondary outcome measures such as gastrointestinal reaction score (postoperative pains, distention, nausea, vomiting), acupuncture sensation evaluation scale, laboratory test, postoperative hospital stay, quality of life, readmission rate, and other postoperative complications (fever, pneumonia, wound infection, bleeding, etc.) are assessed and evaluated by our investigators. The first postoperative evaluation of all patients was performed 12–24 h after operation to ensure that the patients were awake.

For gastrointestinal reaction score, postoperative pain will be evaluated regularly at three times a day using the visual analog scale (VAS), and the three scores will be averaged and tabulated with dosage and frequency of patient-controlled analgesia (PCA) and analgesic medication used. The extent of distention is recorded using the Likert scale [17], postoperatively from day 1 to 4. The extent of nausea is recorded using the VAS, postoperative from day 1 to 4. Vomiting will be counted daily.

For Acupuncture Sensation Evaluation Scale, acupuncture sensations are assessed after every acupuncture treatment session through inquiring about patient’s sensations.

For laboratory test, venous blood will also be collected on the day prior to operation, as well as the first and third day after the laparoscopy, to assess the safety of acupuncture base on blood examinations and biochemical indicators.

Postoperative hospital stay is measured from the day of the laparoscopy procedure till the day of discharge.

Quality of life is assessed through the Quality of Life Questionnaire (QLQ-c30), provided to patients prior to operation and 1 month after the operation [18].

For readmission rate, evaluate the readmission of patients 1 month after the operation, record the reasons for readmission in detail, and finally calculate and analyze.

Adverse events include postoperative complications and adverse acupuncture events. Postoperative complications are recorded and evaluated using the Clavien Dindo Classification [19]. Adverse acupuncture events including subcutaneous hematoma, continuous acupuncture afterfeeling, and needle stagnation will be recorded by the assessor.

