Patients between ages 18 and 80 have been included in the study to cover a larger spectrum of the demographics. At the same time, patients after colorectal cancer surgery were completely randomized, and the outcome evaluators and statisticians were blinded, and the reliability of the trials was high. In addition, assessment of gastrointestinal function-related clinical parameters and laboratory tests is done to aid in the evaluation of the efficacy and safety of acupuncture treatments, ultimately providing the basis for the overall evaluation of the effects of acupuncture on recovery of gastrointestinal function from colorectal cancer operations. Clinical parameters for gastrointestinal function include the time of first postoperative flatus, time of first postoperative defecation, time of first fluid intake, hospitalization period, etc. Importantly, laboratory tests such as blood test and biochemical indicators have been included in our study to assess the safety of acupuncture. One of the advantages of our study is the conduct of a follow-up to gather response through the QLQ-c30 to assess patients’ quality of life 1 month after the operation, which will reflect the long-term impact of acupuncture on postoperative colorectal patients.

However, there are limitations to the study. Firstly, ensuring punctual and accurate follow-ups is both an important and difficult task, and insertion of rectal tubes in a portion of our study subjects might cause inaccuracies in reporting the time of first postoperative flatus by the patients. Secondly, the study lacks a sham acupuncture control group, due to difficulties in blinding of study subjects. Lastly, both groups received perioperative nursing guided by ERAS protocol, so the role of acupuncture may be ignored. Despite these limitations, the study should elucidate the general effect of acupuncture on postoperative recovery.

In conclusion, we hope that through rigorous clinical study, statistical evidence of acupuncture in promoting recovery of gastrointestinal function in post-laparoscopy colorectal cancer patients can be demonstrated, providing the basis for the inclusion of acupuncture into ERAS principles and protocols, to encourage the application of acupuncture in the aforementioned condition after conventional surgical procedures.

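### The laboratory values collected to assess the safety of acupuncture fall under a generic two-sided difference test at p ≤ 0.05, which cannot show absence of harm and is insensitive to harm in a few patients

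*Protocol article*

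**What the plan says.** **Purpose.** The Secondary outcomes section has blood drawn on three occasions ("venous blood will also be collected on the day prior to operation, as well as the first and third day after the laparoscopy") and gives the reason: "to assess the safety of acupuncture base on blood examinations and biochemical indicators". The text on biological specimens under Confidentiality {27} is stricter: "The biological samples collected in this study are only used as safety evaluation indicators". The Discussion repeats the safety purpose ("laboratory tests such as blood test and biochemical indicators have been included in our study to assess the safety of acupuncture"), although a sentence just before it takes clinical parameters and laboratory tests together and speaks of both efficacy and safety ("laboratory tests is done to aid in the evaluation of the efficacy and safety of acupuncture treatments").

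**Status.** The laboratory test is listed among the secondary outcomes: "acupuncture sensation evaluation scale, laboratory test, postoperative hospital stay, quality of life, readmission rate".

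**Analysis.** Statistical methods {20a} is headed as covering primary and secondary outcomes. Quantitative indicators are described by mean and SD; frequency tables and percentages are for qualitative indicators. Quantitative data are compared by t test, with a Satterthwaite correction if variances differ, or, if "not in line with normal distribution using Wilcoxon rank-sum test". On sidedness: "The hypothesis test uses a two-sided test and gives the test statistics and the corresponding" p value, with p ≤ 0.05 as significant. Adverse events are to be summarised with severity, outcome and causality, and serious ones presented descriptively. The laboratory values are not named in this section and have no separate rule.

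**The concern.** The stated purpose and the stated method do not match. A two-sided difference test asks whether the arms differ on average. If it returns p > 0.05, the data are compatible with no difference, but also with every difference inside the confidence interval. A safety assessment needs to know how large a harm the data still allow, and a p value does not say.

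The summary also looks in an insensitive place. Laboratory harm in a small trial would most plausibly be a few patients with clearly abnormal values. Such patients move an arm mean only slightly and inflate its SD, and they move a rank sum even less. Mean and SD, the planned description, hide them in the same way.

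At stake is the laboratory part of the safety case, in a trial whose stated objective is to support adding acupuncture to ERAS protocols. The primary outcome and the sample size are not affected.

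**Working it through.** The article gives no power, margin or detection rate for the laboratory values, so there is no figure of its own to reproduce. The size of the harm below is therefore an assumption, shown over a range.

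**Inputs from the article.** 80 patients per arm recruited (68 per arm required by the Sample size section); two-sided test at 0.05; t test or Wilcoxon test.

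**Assumed.** An analyte with SD 1 in both arms when there is no harm; k of the 80 acupuncture patients raised by s SD; controls unaffected.

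**Step 1: what the test is able to see.** The mean difference detectable with 80% power is (1.96 + 0.84) × √(2/80) = 0.44 SD at 80 per arm, and 0.48 SD at 68 per arm. A harm confined to k patients moves the mean by only (k/80) × s. For k = 4 and s = 5 this is 0.05 × 5 = 0.25 SD, well short of 0.44.

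**Step 2: t test, by approximation.** With f = k/80:
- true mean difference: d = f·s
- expected sample variance in the acupuncture arm: v = 1 + f(1 − f)s²
- estimated standard error: √((v + 1)/80), so the critical difference is c = 1.96 × that value
- actual SD of the mean difference with k fixed: √(2/80) = 0.158
- miss probability: Φ((c − d)/0.158) − Φ((−c − d)/0.158)

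For k = 4, s = 5: d = 0.25; v = 1 + 0.0475 × 25 = 2.1875; standard error = √(3.1875/80) = 0.1996; c = 0.391; (0.391 − 0.25)/0.158 = 0.89; miss = 0.81.

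For k = 4, s = 2: d = 0.10; v = 1.19; standard error = √(2.19/80) = 0.1655; c = 0.324; (0.324 − 0.10)/0.158 = 1.42; miss = 0.922 − 0.004 = 0.92.

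**Step 3: simulation.** 5,000 trials per scenario, Welch t test and Wilcoxon rank-sum test, two-sided 0.05, 80 per arm. The miss rate runs from the 5 SD shift to the 2 SD shift:

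| Patients affected | t test misses | Wilcoxon misses |
|---|---|---|
| 3 of 80 | 89-93% | about 94% |
| 4 of 80 | 82-92% | 92-93% |
| 6 of 80 | 64-88% | 88-91% |
| 8 of 80 | 40-80% | 82-86% |
| 12 of 80 | 6-63% | 64-75% |

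The approximation in step 2 agrees with the row for 4 patients. At 68 per arm with 4 affected, the t test misses 80-92% and the Wilcoxon test 92-93%.

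**Step 4: what an interval adds.** If no acupuncture patient of 80 is affected, the one-sided 95% upper limit on the true rate is 1 − 0.05^(1/80) = 3.7%. If 4 of 80 are affected against 0 of 80 controls, the risk difference is 5.0 percentage points. Its Newcombe 95% interval uses the Wilson limits for 4/80 (2.0% to 12.2%) and for 0/80 (0% to 4.6%):
- lower limit: 5.0 − √((5.0 − 2.0)² + 4.6²) = −0.5 points
- upper limit: 5.0 + (12.2 − 5.0) = 12.2 points

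A p value above 0.05 conceals that 12 points of excess harm remain possible; the interval shows it.

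**The case against.** The case on the other side has five parts.

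*No rule equates non-significance with safety.* This stands. A reader might infer that p > 0.05 will be reported as proof of safety, but no section of the article says so. The point is confined to the stated comparison being unsuited to its purpose.

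*The p-value test is not the only safety check.* This also stands. A reader might infer that harm in a few patients would go unseen. Yet all adverse events reported or observed are recorded with causality, complications are graded by Clavien-Dindo, needling harms have their own record form, and a safety officer assesses serious events. This lowers the consequence. It does not remove the point, because the events named there are clinical complications and needling events, and no rule is stated that turns an abnormal laboratory value into an adverse event.

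*Abnormality limits and shift tables belong in an analysis plan that is not shown.* Correct, and their absence is not the finding. The finding is that {20a}, as worded, assigns a test to these values that does not answer the safety question.

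*Counting abnormal patients would not rescue power.* True for another significance test: 4/80 against 0/80 gives a Fisher p of 0.12, and 5/80 against 0/80 gives 0.059. The gain comes from showing counts with intervals, not from a different p value.

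*The laboratory tests also serve efficacy.* One Discussion sentence covers clinical parameters and laboratory tests jointly. Wherever the laboratory tests or samples are mentioned alone with a purpose, that purpose is safety.

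**Conclusion.** The point holds in a limited form. For an outcome collected to assess safety, the article's only stated comparison is a two-sided difference test of averages or ranks, with mean and SD as the description. A non-significant result from it would not support a safety conclusion, and it has little sensitivity to harm in a minority.

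The figure of roughly 80-90% missed by the t test is an illustration, not a property of this trial. It rests on about 4 of 80 patients affected, a shift of 2 to 5 SD, a normally distributed analyte and no effect in controls. With 8 affected the t test misses 40-80%, and with 12 affected 6-63%, so the figure should not be quoted without its scenario.

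This is a cheap improvement to one secondary safety outcome. It neither undermines the trial's safety monitoring as a whole nor touches the primary analysis.

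**What to change.** In Statistical methods {20a}:

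1. Exclude the laboratory safety values from the p ≤ 0.05 rule.
2. For each analyte, report by arm the number of patients whose values move from the preoperative sample to beyond the hospital laboratory's pre-set limits, with the risk difference and its 95% confidence interval.
3. Give the between-arm mean difference with its 95% interval as supporting information.
4. State that a non-significant difference will not be taken as evidence of safety.

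The limits themselves can sit in the analysis plan, provided that they are fixed before the data are compared by arm.

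Cost: a few sentences and a little more tabulation. No new samples are needed, since the preoperative, day 1 and day 3 samples are already scheduled. The downside is a more cautious safety statement, because at 80 per arm the intervals will be wide.

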#### Interim analyses {21b}

There are no interim analyses planned.

#### Methods for additional analyses (e.g., subgroup analyses) {20b}

There are no subgroup analyses planned.

#### Methods in analysis to handle protocol non-adherence and any statistical methods to handle missing data {20c}

The primary outcome will be assessed using an intention-to-treat analysis. Missing data will be reduced to a minimum by using the appropriate measures described above. Mixed models do not require imputations for missing data. If any statistical method is needed to account for missing data in the secondary outcomes, multiple imputation will be used.

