### Criteria for discontinuing or modifying allocated interventions {11b}

Patients can leave the study at any time for any reason if they wish to do so without any consequences. The patient’s participation in this study can also be ended by the investigator if the patient is uncooperative and/or does not attend study visits. The patient data that have been collected up to that moment will be included in the analysis. In case too many data are missing, the patient will be replaced by a new patient. If there are adverse events or postoperative complications, the study will be terminated early. In case of illness, patients will be asked to contact the primary investigator. Patients that are discovered after surgery not to meet the criteria will not receive acupuncture treatment and will be treated according to the standard of care. These patients will be removed from the study. Patient data included up to that moment will be included in the analysis.

Criteria for study termination include the following: ① The pain of acupuncture was intolerable or serious adverse reactions occurred; ② during the treatment, the symptoms worsened or other critical diseases appeared, and the patients could not continue the treatment; ③ researchers found that there were serious safety problems; ④ because of various reasons cannot adhere to the treatment.

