### Outcomes {12}

#### Primary outcome

Time of first postoperative flatus is the study’s primary outcome and is measured as the time period starting from the patient’s return to ward after the laparoscopy procedure till the first passage of flatus. It is obtained through the assistance of family members and caregivers, via inquiry and record of patient’s status.

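### The missing-data plan for time to first flatus relies on a mixed model that is not specified and could not help, so the promised intention-to-treat analysis is in effect complete-case

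*Protocol article*

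**What the plan says.** The Primary outcome section of the protocol article states "Time of first postoperative flatus is the study’s primary outcome" and defines it as "measured as the time period starting from the patient’s return to ward after the laparoscopy procedure till the first passage of flatus". That is one elapsed time per patient.

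Section {20a} gives the between-group tests: "quantitative data in line with normal distribution using the *t* test", with a Satterthwaite correction for unequal variances, and data "not in line with normal distribution using Wilcoxon rank-sum test". It names no mixed model, survival method, censoring rule or score for a patient without a time.

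Section {20c} then says "The primary outcome will be assessed using an intention-to-treat analysis". On missing data it says "Mixed models do not require imputations for missing data", followed by "If any statistical method is needed to account for missing data in the secondary outcomes, multiple imputation will be used". This is the only mention of a mixed model in the article.

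Section {11b} expects early departures. Patients may leave at any time, the investigator may end participation, and worsening symptoms, critical illness and intolerable needle pain are listed as reasons to terminate. Of those who leave or are withdrawn it says: "The patient data that have been collected up to that moment will be included in the analysis". It also replaces patients with too many missing data and removes those found ineligible after surgery.

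**The concern.** The promises and the tools do not fit together. Intention-to-treat requires every randomised patient to count. The named tests need a number from each patient, and a patient who leaves before first flatus supplies only a lower bound. The method invoked to cover such gaps is absent from the analysis section, and the fallback of multiple imputation is not extended to the primary outcome.

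At stake is whether the primary comparison remains randomised. The Abstract links delayed gastrointestinal recovery to obstruction, paralysis and leaks, and {11b} links complications to early termination. Slow recovery and a missing time can therefore share a cause. Patients know their allocation, and only the acupuncture arm can stop because of needle pain, so unequal loss is credible.

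The choice between t test and Wilcoxon test adds to this. It depends on the trial's own data, so whether a mean difference or a rank comparison is primary is not fixed in advance. The sample size rests on a mean difference.

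**Working it through.** The plan gives no rate of missing flatus times, so there is no figure of its own to reproduce on this point. The sample-size arithmetic is a separate matter; only its effect size and standard deviations (SDs) are used here.

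**1. Sections side by side.**
- Primary outcome: one value per patient.
- {20a}: t test, corrected t test or Wilcoxon test; no mixed model.
- {20c}: intention-to-treat for the primary outcome; mixed models said to need no imputation; multiple imputation for secondary outcomes.
- {11b}: data up to leaving are to be analysed.

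For a patient without flatus, the data up to leaving are a censored time. No rule in {20a} or {20c} brings it into the primary test.

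**2. What a mixed model would add.** A mixed model can use incomplete patients because their other measurements of the same outcome inform the missing one. First flatus has no other measurement. In a simulated set of 160 patients with 5 times missing, a model with one value per patient used 155 patients and gave a group difference of -3.62 h, identical to the complete-case difference in means.

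**3. Illustrative size.** Inputs from the Sample size section: target 8 h; SD 12.28 (acupuncture) and 14.57 (control). Assumptions: normal times, and the lost patients are exactly the slowest fraction p of one arm. The fall in that arm's observed mean is SD × φ(z)/(1 − p), where z is the (1 − p) quantile of the standard normal.
- p = 5%: φ(1.645)/0.95 = 0.1031/0.95 = 0.109. Acupuncture 12.28 × 0.109 = 1.3 h; control 14.57 × 0.109 = 1.6 h.
- p = 10%: φ(1.282)/0.90 = 0.1755/0.90 = 0.195. Acupuncture 12.28 × 0.195 = 2.4 h; control 14.57 × 0.195 = 2.8 h.

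Relative to 8 h, the range is 1.3/8 = 17% (rounded from 1.33/8) to 2.8/8 = 35%.

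**4. Effect on the test.** Simulation under the same assumptions, with 80 per arm, control mean 50 h (assumed; it does not affect the difference), 4,000 runs and a two-sided Welch t test at 0.05:

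| True effect | Loss | Mean estimate | Rejection rate |
|---|---|---|---|
| 0 h | none | 0.0 h | 6% |
| 0 h | 5% / 10%, acupuncture only | 1.3 / 2.4 h | 11% / 22% |
| 0 h | 5% / 10%, both arms | -0.3 / -0.4 h | 7% / 9% |
| 8 h | none | 8.0 h | 96% |
| 8 h | 5% / 10%, control only | 6.4 / 5.2 h | 86% / 72% |
| 8 h | 5% / 10%, both arms | 7.8 / 7.5 h | 96% / 96% |

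Unequal loss does the damage. Equal loss hardly moves the estimate, although it still raises the null rejection rate somewhat under this extreme mechanism.

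**The case against.** The strongest reply is that most patients will probably pass flatus while still observed in hospital, so few times may be missing. With nearly complete data a t or rank test is valid. The article is also condensed, and scoring and censoring rules usually belong in the analysis plan. The first part stands as a limit on size. The second does not remove the point, because the article does state a missing-data method for its analysis, and that method conflicts with its own list of tests.

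Several stronger readings are tempting but not supported:
- **That 32 of 160 patients (20%) would be absent from the primary test.** The 20% is an overall dropout allowance in a trial followed to one month. A patient lost after passing flatus still has the primary outcome.
- **That the bias could reach 4.8 h**, for example by losing 10% of an arm whose times average 48 h longer (0.10 × 48). That group alone would contribute 0.10 × 0.90 × 48² = 207 h² of variance. The planned control variance is 14.57² = 212, leaving almost nothing for the other 90%; the acupuncture variance is 12.28² = 151, which is less than 207. A heavier tail, or SDs that already exclude such patients, would loosen this, but the documents show neither.
- **That a Wilcoxon test can never include these patients.** It can under a worst-rank rule; none is stated.
- **That a mixed model has no possible use in this trial.** It could serve the repeated daily pain, distention and nausea scores, though none is specified for them.
- **That all intensive-care cases are lost.** Severe complications needing intensive care are an exclusion criterion, and envelopes are opened only after eligibility is confirmed, so some such cases never enter.

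The lack of a promised confidence interval is ordinary detail for an analysis plan and forms no part of this point.

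**Conclusion.** The contradiction is established from the text alone. The primary outcome has no working missing-data method, and the tests as written turn the intention-to-treat label into a complete-case analysis. The resulting bias cannot be quantified, because it depends on how many patients lack a flatus time and whether that differs by arm. The illustrative 1.3 to 2.8 h assumes normal times, the plan's SDs and loss of exactly the slowest 5 to 10% in one arm only; it shows what could happen and is not a forecast. If losses are rare or balanced, the effect on the estimate is small. Correction is still warranted: the primary analysis cannot be carried out as described, and the choice among tests should not wait for the data.

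**What to change.** Delete the mixed-model sentence, or attach it to named repeated secondary measures. Then fix one primary analysis over all randomised patients. A suitable choice is:
- a log-rank test with Kaplan-Meier curves, timed from return to the ward;
- patients without flatus censored at their last observation;
- events that preclude flatus counted as flatus not achieved up to a stated common horizon;
- a restricted-mean difference in hours over that horizon, to link the result to the 8 h target.

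Censoring for other early departures still assumes that leaving is unrelated to imminent recovery; the text should say so. A Wilcoxon test with a pre-stated worst-rank rule is an acceptable minimum. Keep the Welch t test, without preliminary tests, as a sensitivity analysis. Reconcile the replacement and removal rules in {11b} with intention-to-treat.

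The cost is wording in {20a}, {20c} and {11b}, and making sure the case report form records when a patient was last known not to have passed flatus. The statistical downside is a small loss of efficiency if the times turn out normal and complete.
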